## Methods

### Study Design and Procedure

The study is a single-blind, randomized controlled trial. The researchers will be blinded for the treatment’s allocation during the duration of the trial. Owing to the nature of the intervention, neither the participants nor the program staff can be blinded to the allocation type. Patients will be recruited at the outpatient University Hospital's CR Center. The study will conform to the Consolidated Standards of Reporting Trials (CONSORT) guidelines for nonpharmacological interventions [20]. After being invited to participate in the study, the volunteers will sign a consent form and will be randomized into 2 different groups: traditional CR (mostly supervised) and home-based CR (mostly unsupervised). The randomization will be made in blocks of 4 volunteers at a time [21]. A blinded researcher will evaluate the participants before and after the intervention and will collect the data into a database.

This study protocol is in accordance with the most recent version of the World Medical Association Declaration of Helsinki. This study was approved by the Ethics Committee in Research of the Universidade Federal de Minas Gerais, Brazil and was registered under the CAAE 51528615.3.0000.5149, on February 23, 2016. The CONSORT flowchart is reported in Figure 1.

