### Groups

#### Traditional and Face-to-Face Cardiac Rehabilitation as Control Group

The control group will receive, in person, the usual program consisting of supervised exercises and health educational activities at the CR center. This intervention will last for 12 weeks, with a total of 60 sessions: 24 supervised and 36 home sessions (5 exercise sessions per week). The participants of this group will be instructed to complete a training diary, with information regarding the frequency and intensity of exercises (using a scale of perceived exertion) as well as the presence of symptoms during or after exercises. The same information will be registered in their individual file while exercising at the CR center.

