#### Secondary Outcomes: Functional Capacity, Cost, Morbidity, Control of Risk Factors, Heart Health Behaviors, and Usability

Changes in the functional capacity will be analyzed using the incremental shuttle walk test (ISWT), a walking test that evaluates the functional capacity through the analysis of the walked distance [27].

The cost analysis and morbidity variables will be evaluated after 3 months and after 3 and 6 months, respectively, in both groups. The analysis of the programs’ cost will be made by calculating the total sum of each procedure in the 2 groups, considering the hospital’s payments table for procedures and services. Morbidity will be evaluated through a survey to identify the number of hospitalizations, complications, and the presence of adverse clinical events during the study period.

Resting blood pressure, measured in mm Hg, and waist circumference, measured in cm, will be analyzed. Waist circumference will be assessed at the superior border of the iliac crest, in accordance with the standardized guideline [28]. Alterations in fasting glucose (mg/dL), glycohemoglobin (%), and total cholesterol (mg/dL) values will be analyzed before the CR program and reanalyzed after 3 and 6 months.

Other behaviors will be assessed using psychometrically validated scales. Quality of life will be assessed using the Short Form 36 questionnaire [29], depression by the Patient Health Questionnaire-9 [30], the physical activity level using the Duke Activity Status Index Score [31], and the level of knowledge by the Coronary Artery Disease Education Questionnaire-Short Version [32].

Alterations in fasting glucose, glycohemoglobin, total cholesterol values, measures of resting blood pressure, waist circumference, quality of life, depression, physical activity level, functional capacity, and knowledge about coronary diseases will be evaluated at the beginning and after 3 and 6 months of the intervention in both groups. The assessment schedule is reported in Table 1.

The usability of the equipment used in the home-based group will be verified through the System Usability Scale after 3 months [33].

**Table 1 table1:** Schedule of outcome assessments for control and home-based groups.

Outcome measures			Control group			Home-based group		
			Baseline	3 months	6 months	Baseline	3 months	6 months

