### Sample Size

On the basis of previous CR studies [34] and on our 7-year experience in providing rehabilitation services in a university hospital, we estimated a compliance of 70% in the control group and of 96% in the home-based group. We calculated that for an alpha significance level of 5% and a power of 80% in the Fisher exact *t* test, the sample size of each group should be at least 36 volunteers. We also calculated the sample size for the secondary outcome, the functional capacity (ISWT), considering an arbitrary small size effect of 0.25. To detect a statistically significant difference within and between groups (2×2), at least 34 volunteers in each group are needed, keeping the same values of alpha and power. After a pilot study with 10 subjects in each group, the sample calculation will be performed again. All the calculations were made using the G Power 3.1.9.2. software (Franz, Universitat Kiel) [35].

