### Statistical Analyses

Data will be presented as a measure of the central tendency and dispersion. Data distribution will be analyzed using the Shapiro-Wilk test. All statistical analyses will be performed considering the intention-to-treat analysis and a per protocol basis to mitigate bias. The comparison between groups of the primary outcome will be made using the Fisher exact test, considering that the expected frequency of noncompliance of the home-based group may assume a value lower than 5%. Differences between groups and at the follow-up 3 and 6 months after the intervention, in addition to the interaction effect, will be analyzed using the generalized estimation equations [36]. In all models, the endpoint variable will be analyzed as a dependent variable and the variable at baseline and after 3 months as independent variables. An alpha value of 5% will be considered for statistical significance. Post hoc tests will be performed where significant differences are observed between the groups.

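### The secondary-outcome models use the 3-month value as both an outcome and an independent variable, so read literally their 6-month group coefficient is not the total effect of the programme

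*Protocol article*

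**What the plan says.** Two consecutive sentences in the Statistical Analyses section of the protocol article define the secondary analysis.

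- The first sets the target for generalized estimating equations (GEE): "Differences between groups and at the follow-up 3 and 6 months after the intervention, in addition to the interaction effect".
- The second fixes the variables for every model: "the endpoint variable will be analyzed as a dependent variable and the variable at baseline and after 3 months as independent variables".

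The Secondary Outcomes section lists ten measures with a baseline value: functional capacity by shuttle walk, blood pressure, waist, glucose, glycohemoglobin, cholesterol, quality of life, depression, physical activity and knowledge. These "will be evaluated at the beginning and after 3 and 6 months of the intervention in both groups". Table 1 shows the same schedule.

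On timing, the control group section says "This intervention will last for 12 weeks, with a total of 60 sessions", and the home-based section gives the same length. The 3-month visit is therefore the end of the programme. According to the Intervention section, patients are afterwards only encouraged to keep exercising until the re-evaluation.

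**The concern.** A baseline value precedes randomisation, and adjusting for it is sound. The 3-month value follows 12 weeks of the allocated programme and is partly a result of it. With that value held fixed, the group coefficient compares patients who reached the same level at the end of treatment. It no longer measures what being allocated to home-based rather than traditional rehabilitation does to the 6-month level.

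The two sentences also do not fit together. If the 3-month value is a predictor, the model cannot also estimate the 3-month group difference or its interaction with visit.

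Effectiveness is a stated objective, and the shuttle walk has its own sample-size calculation. The contrasts at stake are the between-group comparisons of the ten repeated measures. A difference that lasts could be understated, and one that fades could be reported as favouring the other programme.

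**Working it through.** **The plan's own figure.** The article states no figure for a 6-month group effect, SD or correlation. The related figure is the primary sample size: "we estimated a compliance of 70% in the control group and of 96% in the home-based group", leading to "the sample size of each group should be at least 36 volunteers". Exact enumeration of a two-sided Fisher test at alpha 5% gives power of 79.6% with 35 per group and 81.3% with 36, so 36 reproduces. It is used below only as the group size.

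**Inputs taken from the article.** Two groups of 36; visits at baseline, 3 and 6 months; 6-month value as dependent; baseline and 3-month values as independent.

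**Inputs assumed.** Within-group SD of 1 at each visit; correlation r from 0.5 to 0.8, either equal between all visits or first-order autoregressive (AR(1)); a linear model with slopes common to both groups.

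**Formula.** With baseline balanced by randomisation, the 6-month value is

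Y6 = a + d6·group + b0·(Y0 − m0) + b3·(Y3 − m3 − d3·group) + error,

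where m0 is the baseline mean and m3 the control-group mean at 3 months. Collecting the group terms gives

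expected group coefficient = d6 − b3·d3.

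The slope is b3 = (r36 − r03·r06)/(1 − r03²), where the subscripts name the two visits correlated.

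- Equal correlation: b3 = (r − r²)/(1 − r²) = r/(1 + r). At r = 0.7 this is 0.7/1.7 = 0.41.
- AR(1): b3 = (r − r³)/(1 − r²) = r. At r = 0.7 this is 0.70.

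**Results.** Each cell gives the expected coefficient under equal correlation / AR(1), in SD units.

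| True effects | r = 0.5 | r = 0.7 | r = 0.8 |
|---|---|---|---|
| Slope b3 | 0.33 / 0.50 | 0.41 / 0.70 | 0.44 / 0.80 |
| Sustained: d3 = 0.50, d6 = 0.50 | 0.33 / 0.25 | 0.29 / 0.15 | 0.28 / 0.10 |
| Waning: d3 = 0.50, d6 = 0.10 | −0.07 / −0.15 | −0.11 / −0.25 | −0.12 / −0.30 |
| Opposed: d3 = −0.20, d6 = 0.50 | 0.57 / 0.60 | 0.58 / 0.64 | 0.59 / 0.66 |
| Late only: d3 = 0, d6 = 0.50 | 0.50 / 0.50 | 0.50 / 0.50 | 0.50 / 0.50 |

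Worked example for a sustained effect at r = 0.7: 0.50 − 0.412 × 0.50 = 0.294 under equal correlation, and 0.50 − 0.70 × 0.50 = 0.15 under AR(1).

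**Simulation check.** 4000 trials per scenario, 36 per group, r = 0.7, linear regression of the 6-month value, two-sided 5% test.

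| True effects, correlation | Baseline only: estimate, rejections | Baseline and 3 months: estimate, rejections |
|---|---|---|
| 0.50 and 0.50, equal | 0.505, 83% | 0.301, 44% |
| 0.50 and 0.50, AR(1) | 0.500, 66% | 0.152, 13% |
| 0.50 and 0, equal | 0.001, 5% | −0.203, 23% |
| 0.50 and 0, AR(1) | 0.000, 6% | −0.348, 48% |
| 0 and 0.50, equal | 0.502, 83% | 0.504, 90% |

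Baseline-only adjustment recovers the true 6-month effect each time. The simulated estimates agree with the formula to within simulation error.

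**The case against.** **The sentence may be loosely worded.** GEE with group differences at 3 and 6 months and an interaction is a repeated-outcome model. The next sentence does not list group, visit or interaction, so it is not a full specification. Baseline and 3 months might be meant as time levels. That reading is possible, but the sentence does not say it: it names the variable at those two times as independent, separately from the endpoint, and leaves out 6 months, which a list of time levels would include. What stands is that the conflict between the two sentences is certain, while the fitting of the biased model is an inference from the literal text.

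**The bias may be small.** The article cites evidence that home and centre programmes have comparable effects on risk factors and exercise capacity. If the 3-month difference is near zero, so is the bias. This stands, and it is why no single figure can be given.

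**The check is not the planned GEE.** It uses a single-endpoint linear model. That is the literal content of the sentence for a continuous 6-month endpoint, but the rejection rates remain illustrative.

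**The main result is safe.** Compliance is compared at 3 months by Fisher's exact test and uses none of these models. Cost and usability are assessed only at 3 months. This also stands.

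A reader might infer that the 6-month effects are always pulled toward zero. The documents do not support that. Shrinkage needs 3- and 6-month effects in the same direction and a positive slope, and the article fixes neither. Opposed effects are inflated, and a null 6-month effect preceded by a 3-month difference yields a false one.

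**Conclusion.** The sentence is wrong as written and contradicts the one before it. Read literally, the 6-month coefficient estimates d6 − b3·d3. With a positive slope:

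- it is shrunk when the two effects agree in direction;
- it reverses sign when the effect wanes so far that d6 falls below b3·d3, for example below 41% of the 3-month effect at r = 0.7 under equal correlation;
- it is inflated when the effects oppose each other.

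It equals the total effect only if d3 or b3 is zero.

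The size rests wholly on assumed correlations and effects. For a sustained 0.50 SD effect and r from 0.5 to 0.8, 67% to 56% of it is retained under equal correlation and 50% to 20% under AR(1). For an effect of 0.50 SD at 3 months that is gone by 6 months, r = 0.7, a false difference of about −0.20 or −0.35 SD appears, and a 5% test rejects in about 23% or 48% of trials. The consequence is confined to the repeatedly measured secondary outcomes; the primary compliance analysis and its sample size are unaffected.

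**What to change.** Rewrite the second sentence so that, for each outcome measured at all three visits, the 3- and 6-month values are the repeated dependent values in the planned GEE. The independent variables are group, visit, group-by-visit and the baseline value only. Report the group difference at each visit with its confidence interval. This also supplies the 3-month difference and the interaction that the first sentence asks for.

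If the authors want to know how patients fare from 3 to 6 months given their 3-month level, that can be a separate, labelled analysis that is not presented as the effect of the programme.

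The cost is one sentence. No new data and no other estimation method are needed. The article describes recruitment as still open and the analyst as blinded, so on its account the change could be made and dated before any unblinded analysis.

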## Results

Recruitment started in February 2018 with an end date of October 2019. Between February 2018 and August 2019, 51 patients have consented to participate in this trial, and all of them were evaluated after 3 months. The recruitment was slower than estimated because of the reform of the CR sector during this period.

## Discussion

### Principal Findings

Various studies showed that home-based CR programs overcome the traditional participation barriers and promote effects comparable with CR outpatients regarding the mortality, risk of recurrent coronary event, cardiovascular risk factors, and exercise capacity [16-34]. These studies were mostly performed in the middle- and high-income countries, where the use of technologies is viable without great difficulties.

In LMICs, the use of technologies for CR programs is oftentimes not feasible. Thus, our study is important because it is performed in a public hospital in a country with a prevalence of low-income, low-schooling population, which have difficulties in using new technologies.

To our knowledge, this is the first study performed in Brazil that contemplates a remote CR program using an accessible and low-cost technology. If positive results are obtained, this study will contribute to establish a new model of remote CR, where the participants will be able to perform the prescribed exercises near home, at convenient times, minimizing the barriers for access to CR and reaching populations that frequently would not have accessibility to CR programs.

We believe that this study has a high potential to improve the care of patients affected by CAD in Brazil as well as in other countries from Latin America.

### Strengths and Limitation of This Study

An important strength of this study is the first to examining the potential of assessing CR remotely in Brazil using an accessible and low-cost technology. There is currently insufficient evidence on the effectiveness of home-based CR programs in LMICs, so the results may be used to improve the care of patients with coronary diseases in Brazil as well as in other LMICs. The limitation of this study is that it enrolls participants with low and moderate risk. Therefore, the results of this study may be used in the practice of cardiovascular rehabilitation within certain limitations.

## Abbreviations

CAD: coronary artery disease
CONSORT: Consolidated Standards of Reporting Trials
CR: cardiac rehabilitation
CVD: cardiovascular diseases
ISWT: incremental shuttle walk test
LMIC: low- and middle-income country
